## Abstract

**Objectives:**

This study aims to evaluate the clinical impact of introducing an Enhanced Recovery After Surgery (ERAS) protocol in the management of patients undergoing cytoreductive surgery (CRS), with or without hyperthermic intraperitoneal chemotherapy (HIPEC). By addressing a population at high risk of postoperative complications and delayed recovery, the study seeks to determine whether ERAS can improve short-term outcomes, optimize perioperative care, and promote faster and safer recovery in a standardized, evidence-based manner across multiple centers.

**Methods:**

The EPICH study is a multicenter, prospective, interventional trial conducted across 20 centers in Italy. A total of 300 patients undergoing CRS±HIPEC will be enrolled in two sequential phases: standard perioperative care followed by ERAS protocol implementation. The primary endpoint is the mean hospital length of stay (LOS). Secondary endpoints include postoperative complications, ICU admission, readmission rates, bowel function recovery, mortality, and patient-reported quality of recovery. The ERAS protocol includes prehabilitation, anemia and nutritional optimization, intraoperative fluid and pain management, and early mobilization and oral feeding. Data will be analyzed using random-effects linear models to account for center-level variation and confounding factors.

**Results:**

Preliminary evidence suggests that the ERAS protocol may help reduce mean hospital LOS, postoperative complications, and ICU stays, as well as support faster bowel recovery and improved patient-reported outcomes—findings that this study seeks to validate.

**Conclusions:**

The EPICH study could provide robust evidence supporting the adoption of ERAS as the standard of care for patients undergoing CRS±HIPEC, with potential benefits in terms of improved recovery, reduced complications, and decreased healthcare resource utilization.

## Background

The E.R.A.S (Enhanced Recovery After Surgery) program was developed with the objective of optimizing the care pathway of patients who are candidates for elective major surgery, with the aim of facilitating an earlier post-surgery recovery. The protocol is comprised of a set of strategies and procedures based on scientific evidence from various disciplines beyond surgery, including anesthesia, nutritional care and rehabilitation. The various specialist must interface and coordinate with each other in order to minimize perioperative stress and promote a rapid recovery of physiological functions in the postoperative period. It has been demonstrated that this multimodal approach, which originated in colorectal surgery in the second half of the 1990s, has reduced morbidity rate, convalescence and length of stay (LOS) in standard colorectal operations [1], [2], [3], [4]. Furthermore, it has been adopted by other surgical disciplines, such as gynecology and urology [5], [6], [7].

Cytoreductive surgery in combination with hyperthermic intraperitoneal chemotherapy (HIPEC) has now been established as a valid therapeutic option for patients with peritoneal surface malignancies. It represents the gold standard for the treatment of pseudomyxoma peritonei and peritoneal mesothelioma and may also be a potential strategy for selected patients with peritoneal metastasis of ovarian or gastrointestinal origin. The objective of surgical cytoreduction is the removal of macroscopically visible disease (or the reduction of it to leave minimal residual disease). The combination with HIPEC allows for the removal of any microscopic residual disease that may still be present. Despite the well-established benefits of this combined treatment, the literature reports non-negligible postoperative morbidity and mortality rates due to the extent of the surgical procedures and the addition of intraperitoneal chemotherapy, which impedes the healing process and recovery of organ function. A direct consequence of these effects is a slowed recovery of intestinal motility and a prolonged length of hospitalization, which results in higher costs.

The ERAS Society has formalized guidelines for enhanced recovery after surgery for a variety of surgical procedures [8], [9], [10], [11]. Additionally, guidelines for patients with peritoneal surface malignancies undergoing cytoreductive surgery with or without HIPEC have recently been published [12], 13]. A substantial body of evidence demonstrates that the implementation of the ERAS program in this surgical context has resulted in a reduction in postoperative complications and hospitalization times, while concurrently enhancing patient satisfaction [14], [15], [16], [17]. In light of these outcomes, our Institute, where the ERAS program is already routinely employed for elective digestive [18] and gynaecological surgery [19], has expanded this protocol to encompass the perioperative management of patients with peritoneal malignancies.

A survey was conducted at the end of 2023 at 21 Italian referral centers specialized in the treatment of peritoneal surface malignancies. The results demonstrated a high level of interest in the systematic application of the ERAS program in this field (76.2 %). However, various difficulties in the application of the guidelines were also identified, including the high number of items, organizational problems and the low level of evidence in terms of efficacy [20]. In order to develop a suitable protocol, a second survey was conducted with the objective of reviewing all the items proposed in the guidelines and of selecting those that registered a high level of consensus regarding their effectiveness and applicability in this context. A shared ERAS protocol has been identified. The EPICH study is a multicentric interventional pre-post study aimed to evaluate the feasibility of the ERAS approach implementation for patients who are candidates for cytoreductive surgery and HIPEC and to assess its impact on the patients’ outcomes.

## Patients and methods

### Study design

EPICH study is a multicenter, prospective, interventional, cohort study with a pre-post design assessing the perioperative management according to the ERAS protocol in patients with peritoneal metastasis undergoing cytoreductive surgery with or without HIPEC.

Approximately 300 patients will be enrolled in 20 centers over 12 months. In the first period (approximately 4 months, 100 patients planned) the usual perioperative procedures will be described. In the second phase (approximately 8 months, 200 patients expected), the participating centers will apply the defined and agreed ERAS protocol.

The following elements of the ERAS protocol will be monitored during the study: prehabilitation and preoperative counselling, dietary assessment and possible nutritional support, antibiotic prophylaxis and bowel preparation, preoperative fasting management and postoperative resumption of fluid/solid intake per os, management of infusions and intra/postoperative analgesic therapy.

### Population and selection criteria

The EPICH study will recruit patients with peritoneal surface malignancies candidates for cytoreduction surgery, whether or not associated with HIPEC. Eligibility criteria are reported in Table 1.

**Table 1: j_pp-2024-0033_tab_001:** Eligibility criteria for EPICH Study.

Inclusion criteria	Exclusion criteria
– Written informed consent signed prior to procedure – Diagnostic histological/cytological examination of advanced solid tumour with documented peritoneal disease from the following neoplasms: – Tumour of gynecological origin – Gastric cancer – Tumour of intestinal origin – Age between 18 and 75 years – Performance status according to ECOG≤1 – ASA score ≤3	– Lack of signed written informed consent – ASA score >4 – Palliative or other unplanned surgery – Severe renal/liver/cardiac failure; a recent myocardial infarction, or severe arrhythmia are excluded from the study. – Immunosuppression, whether due to underlying disease or immunosuppressive therapy, or primary immunodeficiency.

## Intervention

### Establishing an ERAS team

In order to comply with the standards set forth by the ERAS program, a team comprising surgeon, anesthetist, dietician and nurse (the physiotherapist intervenes at the request of the medical staff if necessary) must be assembled. This team is responsible for implementing the protocols and principles set forth in the program, with the aim of facilitating early recovery. A structured implementation phase, including training and adaptation of workflows, will precede the ERAS intervention. This will ensure a standardized and effective transition across participating centers.

The protocol precisely follows each recommendation of the official guidelines published by the ERAS Society for the perioperative management of patients undergoing cytoreductive surgery with or without HIPEC. Figure 1 illustrates the flowchart of pre-, intra-, and postoperative items.

**Figure 1: j_pp-2024-0033_fig_001:**
[figure not shown]
Structured ERAS pathway for patients undergoing CRS ± HIPEC: pre-, intra-, and postoperative phases.

### Pre- operative phase management

–Pre-operative counselling (to be conducted by the team during a designated meeting): the patient is informed of the details of the ERAS program which encompasses corrective interventions aimed at cessation of smoking and alcohol abuse.–Screening for anemia: it should be conducted at least 4 weeks prior to CRS ± HIPEC. In the event that anemia is identified, prompt medical therapy with oral or intravenous iron, folate/vitamin B12 implementation or treatment with erythropoietin should be recommended. Preoperative transfusions should be considered in cases of severe refractory situations.–A prehabilitative exercise program, preferably integrated with other interventions (nutritional or anxiety control), should be initiated.–Assessment of nutritional status based on the Malnutritional Universal Screening Tool (MUST). In malnourished patients or patients at risk of malnutrition, nutritional and protein support (oral>enteral>parenteral) should be routinely indicated for at least 5 days, and in the case of severe malnutrition, up to 14 days. In all patients, pre-operative immunonutrition administration for 5–7 days before surgery may be indicated.–Assessment of cardiac function, comprising a cardiological examination and echocardiography.–Comprehensive respiratory assessment, comprising a pulmonary examination and spirometry with DLCo and RV assessment (especially if diaphragmatic peritonectomy is planned); additionally, a screening for obstructive sleep apnea syndrome (OSAS) could be considered.–Screening process for frailty. Frailty is defined as a state of increased vulnerability and impaired return to homeostasis after physiological stress, and is correlated with worse outcomes after major surgery. The Clinical Frailty Scale (CFS) is a comprehensive assessment tool comprising nine levels that classify a patient’s clinical condition from “fit” to “terminally ill”. The CFS has been demonstrated to be an independent predictor of readmission, disability, and mortality. In the event that a patient presents with a frailty score>4, and this score is not amenable to modification, it may be inadvisable to pursue CRS ± HIPEC.–It is recommended that long-acting sedatives and anxiolytics should be avoided prior to CRS ± HIPEC.–Bowel preparation should be performed in conjunction with oral antibiotic decontamination (Neomycin 2 g and Metronidazole 2 g, or similar) exclusively in instances of multiple bowel resections or sigmoidectomy/rectal anterior resection. An enema procedure should be conducted in the evening before surgery. In the event of a sigmoid or rectal resection, perioperative rectal clyster with betadine solution is recommended.–Patients are permitted to consume only clear liquids up to 2 h prior to surgery, while solid foods must be avoided for a minimum of 6 h.–The administration of carbohydrates up to 2 h prior to the induction of anaesthesia has been demonstrated to reduce postoperative insulin resistance and perioperative discomfort, including anxiety.–The administration of antibiotic prophylaxis is contingent upon the guidelines set forth by the respective institution, provided that the regimen is either short-term (within 24 h of surgery) or a single dose (which may be repeated during the surgical procedure).–Antithrombotic prophylaxis: low-molecular-weight heparin should be administered the evening preceding the surgical procedure.–It is recommended that the administration of bevacizumab or other anti-angiogenic drugs be suspended for a minimum of 5 weeks prior to CRS ± HIPEC.

### Intra-operative phase management

–The administration of preoperative multimodal analgesia, comprising paracetamol 1 g and parecoxib 40 mg, is recommended.–Rapid sequence intubation is recommended.–The use of total intravenous anesthesia (TIVA) as an alternative to inhalation anesthesia is recommended as a means of preventing postoperative nausea and emesis.–The prevention of postoperative nausea and vomiting (PONV) in the presence of a Apfel score of ≥2 s is of paramount importance. An Apfel score 2 indicates that prophylaxis is at the discretion of the surgical team. For an Apfel score ≥3, the recommended treatment is dexamethasone 4–8 mg at the time of induction and ondansetron 4 mg at the time of awakening. Post-operatively, ondansetron 8 mg should be administered every 8 h for the first 24 h.–Placement of a peridural catheter (T5-T11, low doses of local anesthetic and opioids) is recommended to be maintained for at least 72 h after CRS ± HIPEC in order to achieve better analgesic control by minimizing the need for intravenous opioid medication. A regional blockade may reduce the stress response by reducing insulin resistance. It may be beneficial to consider the potential use of one or more non-opioid agents, such as dexmedetomidine, magnesium sulphate, lidocaine and ketamine, as a form of supplementation.–It is recommended that protective mechanical ventilation with low tidal volumes be employed.–Urinary catheter positioning.–Naso-gastric tube (NGT) placement and removal at the end of surgery in the absence of risk factors for delayed gastric emptying.–Mechanical thromboprophylaxis (intermittent pneumatic compression) is recommended.–Monitoring of cardiac output through advanced systems, such as EmoSphere and PulsioFlex Monitor.–Monitoring of neuromuscular block.–Prevention of intraoperative hypothermia (defined as a temperature below 36 °C) through active heating devices, a room temperature of 21 °C and/or a closed circuit (fresh gas <1 lt/min), infusions and flushing fluids.–Prevention of intraoperative hyperthermia (defined as a temperature exceeding 41 °C) through active measures, including the use of forced ventilators, cold packs, and environmental settings.–Intraoperative glycemic control to be maintained within the range of 140–180 mg/mL.–Intraoperative restrictive hydration protocol as follows: infusion rate of 5 mL/kg/h should be maintained, with a crystalloid-to-colloid ratio of 1:1 or 2:1. The use of Goal Directed Fluid Therapy (GDFT) or a zero-water balance, based on the patient’s risk profile, is recommended in order to maintain adequate urinary output (1 mL/kg/h). During the perfusion phase, it is essential to increase fluid administration in order to maintain a minimum diuresis of approximately 500 mL/60 min. The administration of vasoconstrictors is advised for patients exhibiting normovolaemic hypotension.–Restrictive policy in terms of blood transfusions, with a threshold hemoglobin level of 8 g/dL.–It is recommended that fresh plasma be avoided in prophylactic use.–Early extubation in the absence of contraindication.

### Post-operative phase management

–In the absence of contraindications, the removal of the urinary catheter should be undertaken as soon as possible, ideally by the morning of the third postoperative day (POD).–The use of laxatives, prokinetics and additional measures (such as coffee and chewing gum) alone or in combination is recommended as a means of preventing postoperative paralytic ileus.–Following the removal of the peridural catheter, a combined analgesic regimen should be initiated, comprising paracetamol, non-steroidal anti-inflammatory drugs and, if necessary, minor opiates.–It is recommended that patients consume clear fluids on the day of surgery, provided there are no contraindications.–A light solid diet may be commenced from the first (POD), provided there are no contraindications. It may be beneficial to consider the addition of oral supplements alongside the usual diet during the initial five PODs.–Food diary to be completed on a daily basis.–Parenteral nutrition with high-protein bags is to be administered for a minimum of 3 days, with a maximum of 7 days permitted. The total volume of infusions should be between 1 and 2 mL/kg/h, with a gradual reduction based on the patient’s oral intake and calories ingested, as assessed by the dietitian.–Postoperative blood glucose monitoring is to be conducted with the objective of maintaining levels between 140 and 180 mg/dL.–Pharmacological thromboprophylaxis with LMWH is to be maintained for up to 4 weeks following surgery.–Early mobilization is to be initiated on POD 2 with the aim of achieving 2 h of out-of-bed activity, and 6 h on the third POD.–The measurement of the criteria for determining whether a patient is fit for discharge should be conducted on a daily basis. The following criteria must be met for a patient to be deemed fit for discharge: absence of nausea or emesis; tolerance to feeding, resumption of bowel function; effective pain management; autonomy in movement and personal hygiene care; absence of clinical or laboratory evidence of postoperative complications.

A surgical examination within 3–5 days and a follow-up dietary examination within 10 days of discharge must be provided. A telephone number must be provided to the patient that can be contacted 24 h a day to report any clinical problems.

## Outcomes

### Primary objective

The main objective is to evaluate the effect of using the ERAS approach on the average length of hospital stay.

### Secondary objectives

The secondary objectives include the assessment of applicability of the ERAS protocol and the consequent effects in terms of postoperative morbidity, length of stay in intensive care unit, reintervention and readmission rate, restoration of bowel function, mortality rate and quality of postoperative recovery.

Table 2 shows primary and secondary endpoints.

**Table 2: j_pp-2024-0033_tab_002:** Primary and secondary end-points.

Primary end-point – Mean length of stay calculated from the day of surgery to the day of discharge, with outliers (duration >95th percentile of the distribution) excluded.
Secondary end-points – Adherence to selected ERAS items, assessed as the proportion of patients managed according to the recommendations of the ERAS protocol – Incidence of postoperative complications according to Clavien-Dindo classification within 30 days after surgery – Mean length of ICU stay (number of nights) – Incidence of reinterventions within 30 days after surgery – Incidence of hospital or emergency department readmissions within 30 days after surgery – Time to recovery of bowel function, calculated from the day of surgery – Incidence of death from any cause within 30 days after surgery – Quality score of postoperative recovery as measured by the QoR-15 questionnaire at approximately 48 h after surgery.

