## Sampzle size

Assuming a standard deviation of LOS, excluding outliers, of 4.5 days, which is assumed to be equivalent across the two periods defined by the application of the protocol (pre and post), the estimated sample of approximately 300 patients provides more than 80 % power to show a mean reduction in the LOS of 2 days, from 10 to 8 days, with a one-sided alpha error of 5 %. This calculation incorporates the clustering of observations within the same center, assuming an intra-cluster correlation coefficient of less than 7 % (rho=0.07).

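### The primary endpoint drops stays above the 95th percentile, so it selects on the outcome and misstates the effect on average LOS whenever ERAS changes the frequency of long stays

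*Protocol article*

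**What the plan says.** The primary objective is to "evaluate the effect of using the ERAS approach on the average length of hospital stay", with no exclusion mentioned. The Methods paragraph of the Abstract also names mean hospital LOS without qualification. Table 2 (Outcomes, Secondary objectives) then defines the primary endpoint as mean LOS from surgery to discharge, "with outliers (duration >95th percentile of the distribution) excluded". It does not say whether the percentile is taken over both periods together or within each period.

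The sample size section carries the same rule into planning: "Assuming a standard deviation of LOS, excluding outliers, of 4.5 days", taken as equal in the two periods, to detect "a mean reduction in the LOS of 2 days, from 10 to 8 days". The trimming is therefore deliberate.

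The Statistical analysis section plans generalized linear mixed models whose family and link follow the distribution of the outcome. Its sensitivity analyses concern adherence and missing data. None analyses LOS in all patients.

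**The concern.** Whether a patient counts towards the primary endpoint depends on that patient's LOS, which is what the intervention is meant to change. These stays are not recording errors. The discharge criteria under Post-operative phase management require that there be no sign of a postoperative complication, and the Background attributes prolonged hospitalization to slow recovery after this surgery. The patients above the cut-off are largely those with complications.

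If ERAS changes how many patients have such stays, the rule discards part of that effect, and it can discard different fractions of the two periods. The estimate then describes a subset defined by outcome. At stake is the main conclusion of the trial: a real benefit may be understated or missed, or a near-zero effect on average stay may look like the planned 2 days.

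**Working it through.** **1. The plan's own figure.** Inputs from Study design and the sample size section: 100 patients before and 200 after, 20 centres (300/20 = 15 per centre), difference 2 days, SD 4.5, intra-cluster correlation 0.07, one-sided 5%.

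- Design effect = 1 + (15 − 1) × 0.07 = 1.98.
- SE = 4.5 × √[1.98 × (1/100 + 1/200)] = 0.776, and 2/0.776 = 2.58.
- Power = Φ(2.58 − 1.645) = 82.5%.

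This agrees with the statement that "the estimated sample of approximately 300 patients provides more than 80 % power". If 5% of patients are dropped (95 and 190), power is 81% to 82%. The sample size is sound for the trimmed endpoint.

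**2. What trimming does to the estimate.** The document gives no LOS distribution, so the shapes below are assumptions. Each row is a large-sample simulation (2 million patients before, 4 million after). Positive values are days of reduction under ERAS. In rows C to F, typical stays are lognormal with SD 4 and mean 10 days, or 8 days after ERAS in C and D. Long stays centre on about 35 days.

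| Scenario | All patients | Common cut-off | Cut-off per period | Dropped before / after, common cut-off |
|---|---|---|---|---|
| A. Lognormal, mean 10 to 8, equal SD (4.5 to 7) | 2.0 | 1.8 | 2.0 | 6–7% / 4% |
| B. As A, SD proportional to mean | 2.0 | 1.3–1.4 | 1.8–1.9 | 8–9% / 3–4% |
| C. Typical stay 2 days shorter, long stays 3% to 8% | 0.6 | 1.8 | 1.1 | 2.4% / 6.3% |
| D. As C, long stays 3% to 10% | 0.0 | 1.5 | 0.6 | 2.0% / 6.5% |
| E. Typical stay unchanged, long stays 3% to 8% | −1.3 | −0.2 | −0.8 | 2.4% / 6.3% |
| F. Typical stay unchanged, long stays 8% to 2% | 1.5 | 0.0 | 0.9 | 8.7% / 3.1% |
| G. Identical distributions | 0.0 | 0.0 | 0.0 | 5% / 5% |

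A cut-off per period drops 5% of each period, which brings the estimate nearer to the all-patient value but does not restore it in rows B to F.

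**3. Error rate when there is no effect.** Simulated trials of 100 against 200 patients, without clustering, one-sided 5%:

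- Common cut-off: about 5%.
- Cut-off per period: about 7.5% (gamma) to 8.5% (lognormal). Each cut-off is estimated from its own sample, and the model's SE (0.51 to 0.54) ignores that. The true SE is 0.57 to 0.63.

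**4. Power without trimming.** The SD in all patients is not given and will probably exceed 4.5. Two treatments of clustering are shown: the design effect of 1.98 from step 1, and the factor 1 − 0.07 = 0.93, which applies if period is compared within centres and the period effect does not vary between centres.

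| Assumed SD | SE, factor 1.98 | Power | SE, factor 0.93 | Power |
|---|---|---|---|---|
| 4.5 | 0.776 | 82% | 0.531 | 98% |
| 5.0 | 0.862 | 75% | 0.591 | 96% |
| 5.5 | 0.948 | 68% | 0.650 | 92% |
| 6.0 | 1.034 | 61% | 0.709 | 88% |

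The SD could be larger still. In the lognormal case of row A, a trimmed SD of about 4.5 goes with an all-patient SD of about 7. Then SE = 7 × √(1.98 × 0.015) = 1.206 and power is about 51%, or SE = 7 × √(0.93 × 0.015) = 0.827 and power is about 78%.

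**The case against.** The strongest defence is that the rule is prespecified and consistent with the planning: the endpoint is a trimmed mean and the SD is for trimmed LOS. The objective speaks of average stay and does not literally say in all patients. This stands as far as it goes, and it clears the sample size of error. It does not make the trimmed contrast an effect on average stay, and no untrimmed analysis is stated beside it.

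A second defence is that trimming works against ERAS if ERAS shortens long stays, as the trial hopes. With a common cut-off that is true of the point estimate (rows A, B and F). It is not a safeguard, because the direction reverses if long stays increase (rows C to E).

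Third, the sizes depend on the assumed shapes. With equal SDs the loss is only about 0.2 day, and rows C and D assume a marked rise in long stays. This also stands: the figures show what the rule can do and are not forecasts.

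A reader might go further than the documents allow in three ways:

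- That harm would be hidden from the study. It would not: complications, reinterventions, readmissions and deaths within 30 days are secondary endpoints without an exclusion on LOS.
- That the 5% error rate is broken. That follows only from a cut-off per period, which the article does not specify.
- That in-hospital deaths are mishandled because LOS ends at discharge. That detail is commonly left to the full protocol or analysis plan, and death is a separate endpoint.

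**Conclusion.** The point holds. Table 2 fixes a primary endpoint that selects patients on their outcome, and the result departs from the effect on average LOS whenever ERAS changes the upper tail. This is a stated rule and not a detail left to another document.

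Under the assumed shapes and a common cut-off, the estimate may lose between a tenth and a third of a true 2-day reduction (1.8 or 1.3 reported). It may add 1.2 to 1.5 days to a true reduction of 0.6 or 0 (0.6 to 1.8, 0.0 to 1.5), or remove a benefit of 1.5 days that comes only from fewer long stays. The bias can go either way and is absent if the two distributions are the same. The distortion is confined to the primary endpoint, and the stated power is correct for that endpoint as defined.

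**What to change.** Define the primary endpoint as LOS in all operated patients, with no exclusion based on LOS. Two workable forms are a mixed model with a family suited to skewed data (gamma or negative binomial with log link), which the Statistical analysis section already permits, or LOS capped at a fixed prespecified day. A cap also alters long stays, but it keeps every patient in the comparison. Keep the mean trimmed at the 95th percentile as a sensitivity analysis and state whether its cut-off is common or per period. If it is per period, use a standard error that allows for the estimated cut-off.

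The change needs no new data, only new wording in Table 2 and the sample size section. The cost lies in the power statement. The planning SD must be restated for untrimmed or capped LOS, and the clustering assumption must be stated with it. At SD 5.0, 5.5 or 6.0, power is about 75%, 68% or 61% with the design effect that reproduces the published figure. It is about 96%, 92% or 88% if period is compared within centres, as the planned mixed model does. The sponsor should settle both before claiming that 300 patients suffice for the all-patient endpoint.
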